## Abstract

**Background:**

Cardiovascular disease is the leading cause of the estimated 11–25 years reduced life expectancy for persons with serious mental illness (SMI). This excess cardiovascular mortality is primarily attributable to obesity, diabetes, hypertension, and dyslipidaemia. Obesity is associated with a sedentary lifestyle, limited physical activity and an unhealthy diet. Lifestyle interventions for persons with SMI seem promising in reducing weight and cardiovascular risk. The aim of this study is to evaluate the effectiveness and cost-effectiveness of a lifestyle intervention among persons with SMI in an outpatient treatment setting.

**Methods:**

The Serious Mental Illness Lifestyle Evaluation (SMILE) study is a cluster-randomized controlled trial including an economic evaluation in approximately 18 Flexible Assertive Community Treatment (FACT) teams in the Netherlands. The intervention aims at a healthy diet and increased physical activity. Randomisation takes place at the level of participating FACT-teams. We aim to include 260 outpatients with SMI and a body mass index of 27 or higher who will either receive the lifestyle intervention or usual care. The intervention will last 12 months and consists of weekly 2-h group meetings delivered over the first 6 months. The next 6 months will include monthly group meetings, supplemented with regular individual contacts. Primary outcome is weight loss. Secondary outcomes are metabolic parameters (waist circumference, lipids, blood pressure, glucose), quality of life and health related self-efficacy. Costs will be measured from a societal perspective and include costs of the lifestyle program, health care utilization, medication and lost productivity. Measurements will be performed at baseline and 3, 6 and 12 months.

**Discussion:**

The SMILE intervention for persons with SMI will provide important information on the effectiveness, cost-effectiveness, feasibility and delivery of a group-based lifestyle intervention in a Dutch outpatient treatment setting.

**Trial registration:**

Dutch Trial Registration NL6660, registration date: 16 November 2017.

## Background

People with a serious mental illness (SMI) have an estimated reduced life expectancy of 11–25 years in comparison to the general population [1–3] This reduced life expectancy is primarily caused by cardiovascular disease [4]. The high risk of cardiovascular disease within this population is mainly due to unhealthy lifestyle behaviour, in combination with the use of antipsychotic medication. People with SMI are more likely to suffer from obesity, hypertension, diabetes and dyslipidaemia [4, 5]. Obesity in particular has been associated with limited physical activity, an unhealthy diet and medication side effects in people with SMI [4]. People with SMI also have less access to healthcare and receive insufficient monitoring and therapy for cardiovascular risks [4–8].

In 2014, the NICE U.K. guidelines of prevention and management of psychosis and schizophrenia in adults were updated [9]. These guidelines recommend that cardiovascular risks should be regularly monitored and healthy eating and physical activity programs should be offered to people taking antipsychotics [9]. In 2015, the multidisciplinary Dutch guidelines for lifestyle and somatic screening in persons with SMI were published to stress the importance of physical health and a healthy lifestyle in persons with SMI [10]. These guidelines likewise mention the significance of lifestyle interventions in daily care in order to reduce somatic health problems in this population.

Even though some studies show mixed results, research indicates that lifestyle interventions might be effective in stimulating healthier lifestyle in people with SMI [11–13]. The STRIDE study - conducted in a community setting in the U.S. - examined a 12-month lifestyle program designed to promote weight loss and reduce cardiovascular risks in people with SMI taking anti-psychotic medication through a healthy diet and increased physical activity [14]. The STRIDE program improved weight, fasting glucose and health-related self-efficacy [15, 16].

It is possible that mental health care workers currently lack sufficient knowledge, techniques and resources to address healthy lifestyle change in order to follow these guidelines in busy and demanding daily practice. Therefore, health care practice needs an innovative approach that is practically feasible for mental health care workers and effectively stimulates healthy lifestyle behaviours among people with SMI.

In the Netherlands, the majority of people with SMI who are living at home receive treatment by Flexible Assertive Community Treatment (FACT) teams. Care from FACT-teams includes illness management, symptom treatment, guidance and practical assistance in daily living, rehabilitation and recovery support [17, 18]. There is little research available regarding an effective lifestyle intervention implemented in Dutch psychiatric ambulatory service. It is unknown whether a lifestyle intervention would be feasible, effective and cost-effective within FACT-team regular care and could effectively contribute to lifestyle changes in this population. Therefore, this study will aim to evaluate the effectiveness and cost-effectiveness of a lifestyle intervention in persons with SMI in Dutch FACT-teams in comparison to usual care; the SMILE (Serious Mental Illness Lifestyle Evaluation) study.

## Methods

### Study design

We will perform a pragmatic multi-centre cluster randomized controlled trial including an economic evaluation from a societal perspective. Follow-up will be 1 year.

### Setting

We will recruit approximately 18 FACT-teams from different mental health care organisations throughout different regions in the Netherlands. To recruit these FACT-teams, we will approach several teams with brief information about the study. If a FACT-team is interested in the study, research staff will provide a presentation for all the members of the FACT-team. Based on this presentation, teams will decide if they are interested in joining the study or not. All FACT-teams will have be certified as “FACT” by the Certification Center ACT and FACT at the beginning of the study.

### Participants

The study population will consist of adult people with SMI, age ≥ 18, a body mass index ≥27, treated by FACT-teams, who in addition are able and willing to participate in the intervention and sign informed consent. A potential participant who meets any of the following criteria will be excluded from participation: contra-indications (to be assessed by the coordinating mental health professional or treating physician) for participation due to acute psychiatric crisis or somatic disease (e.g. bariatric surgery, cancer, heart attack or stroke); individuals with cognitive impairment sufficient to interfere with their ability to provide informed consent, complete study questionnaires, or participate in a group intervention; women who are pregnant, breastfeeding or planning for a pregnancy during the course of the study; participants who are not able to communicate in the Dutch language. All participants will receive 10 Euros for each of the measurements performed at baseline, 6 months and twelve months.

### Randomisation

FACT-teams will be randomly allocated to serve as intervention (where the SMILE lifestyle intervention will be given) or control FACT-teams (where care as usual will be continued). Cluster-randomization will be applied in order to avoid contamination between the intervention and control groups. Randomisation will be performed on the level of mental health care centres to optimize the comparability between FACT-teams in order to reduce bias. Randomisation will be performed by a statistician otherwise not involved in the study. All measurement assessments will be performed by trained research assistants and trained mental healthcare staff from the corresponding mental health care centre. They will use the same standardised protocols for all measurements. Blinding of health care workers from FACT-teams and participants is not possible due to the nature of the intervention.

### Recruitment

To recruit eligible participants, all FACT-teams make a list of potentially eligible participants. The list will be assessed by the coordinating mental health professional for any contra-indications. Potential participants will be approached by the mental healthcare staff from the corresponding FACT-team with information about the study. Before the first measurements take place, the participant will be asked to sign informed consent. An overview of the study design and patient flow is presented in Fig. 1.

**Fig. 1 Fig1:**
[figure not shown]
Overview of the study design and participant flow

### Intervention

The SMILE intervention is primarily modelled after the STRIDE intervention developed by Green et al. [15]. The STRIDE lifestyle intervention is modified for persons with SMI and is based on the PREMIER lifestyle intervention with the DASH (Dietary Approaches to Stop Hypertension) dietary pattern (18–24), both developed for people without mental illnesses. It incorporates behaviour change theories such as the trans theoretical model [19, 20] and motivational theory [21–23]. The SMILE intervention primarily aims at a healthy diet and increased physical activity. The intervention will be given by trained mental health care workers.

The intervention will last 12 months and consists of an initial intervention (first 6 months) and a maintenance phase (second 6 months).

#### Initial intervention

During the first phase, participants will follow weekly 2-h group sessions during the first 6 months. In the group sessions major focus is on topics such as nutrition, increased (moderate) physical activity and lifestyle changes. Topics such as sleep, stress, effects of mental health on behavioural life-style changes, effect of medication use on weight gain, influence of the social environment on life-style behaviour, self-monitoring and goal setting concerning life-style activities are integrated within the program. In each session, participants make their own personal goals, thus tailoring the intervention to the needs, possibilities and motivation of the participant. Contacts will be collaborative, discussing lifestyle change efforts, with guided problem solving. Thirty minutes of the 2-h group sessions will be spent on a physical exercise activity. For each session group leaders will use the SMILE protocol handbook, which describes the content of the intervention.

#### Maintenance phase

The maintenance phase includes 6 months of group sessions, with monthly 2-h group sessions focusing on maintaining weight loss. Sessions will be supplemented with monthly individual telephone sessions and/or email contact with group leaders.

#### Adherence

Intervention group sessions not attended (no-shows) will be assessed by the staff of the according FACT-team. Researchers will visit group sessions of all participating teams in order to improve adherence to the intervention.

### Usual care

Mental health care workers from FACT-teams in the control group will not receive any training. They will provide care as usual.

### Training of mental health care workers

The mental health care workers from the FACT-teams randomised to the intervention group will follow a two-day training. At least two mental health workers of each team will receive the training. They will function as role models for their colleagues within the FACT-team on the subject of lifestyle for persons with SMI and will be the group leaders of the group sessions. The training will consist of: (a) consequences of an unhealthy lifestyle including determinants of increased weight and cardiovascular risks for persons with SMI and medication side effects, (b) elements of motivational interviewing and (c) components of the lifestyle intervention (including contents of group sessions, nutrition components and physical activity guidelines), and (d) a workshop in which different group sessions are rehearsed and reviewed. In addition, attention is given on how to inform and motivate potential participants in joining the lifestyle intervention. The training will be set up and given by two highly experienced trainers with ample expertise on the subject of lifestyle within mental health care and more specifically in FACT-teams. FACT-teams can decide which health care workers will be trained for the intervention. This is done to promote a bigger resemblance to general care and enhance the generalisability of the study.

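### Only teams already randomised to the intervention are trained to motivate patients to join, so recruitment effort, and with it the patients enrolled, can differ by arm

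*Protocol article*

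**What the plan says.** The protocol article randomises teams, not patients (Randomisation): "FACT-teams will be randomly allocated to serve as intervention (where the SMILE lifestyle intervention will be given) or control FACT-teams". The same section says of masking: "Blinding of health care workers from FACT-teams and participants is not possible due to the nature of the intervention".

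Recruitment lies with the teams (Recruitment): "To recruit eligible participants, all FACT-teams make a list of potentially eligible participants". The coordinating professional checks the list for contra-indications, and then "Potential participants will be approached by the mental healthcare staff from the corresponding FACT-team with information about the study". Consent is placed before the first measurements but is not placed relative to randomisation.

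On training, the section Training of mental health care workers says "The mental health care workers from the FACT-teams randomised to the intervention group will follow a two-day training" and later adds "In addition, attention is given on how to inform and motivate potential participants in joining the lifestyle intervention". Under Usual care the counterpart is "Mental health care workers from FACT-teams in the control group will not receive any training".

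The inclusion criteria (Participants) require patients in both arms to be "able and willing to participate in the intervention and sign informed consent".

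The Statistical analysis section plans intention-to-treat analysis, multivariable correction for prognostic variables that it does not name, and correction for demographic variables that turn out unequal.

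**The concern.** In a cluster trial, randomisation balances the teams. It balances the patients only if they are identified and enrolled without regard to the arm. Here one arm's staff are coached to inform and motivate people to join, while the other arm's staff are not coached and have no programme to offer. If that coaching acts on recruitment, the two patient samples can differ in motivation or readiness to change before treatment starts.

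The primary outcome is weight loss, which plausibly depends on motivation. The 12-month difference could then mix a selection effect with the treatment effect. Intention-to-treat analysis keeps the groups as enrolled and cannot correct how they were enrolled. A larger sample would not remove the bias either.

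**Working it through.** **Order of events**

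The article gives no figure for this point, so the first check is to read the sections together.

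1. The trainees belong to teams already randomised to the intervention (Training).
2. The people they learn to motivate are still prospective participants (Training).
3. Willingness to take part in the intervention is a condition of trial entry (Participants). In an intervention team, motivating someone to join the programme is therefore part of bringing that person into the trial.
4. Team staff do the listing and the approach (Recruitment) and cannot be blinded (Randomisation).
5. Control teams receive no training (Usual care).
6. Nothing in the text places listing or consent before allocation, or assigns recruitment to someone unaware of it.

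Steps 1 to 3 imply that at least some intervention-arm recruitment follows a known allocation. Step 5 makes the recruitment effort unequal. This is an inference: the sequence is not stated, and Fig. 1, to which the article refers for patient flow, is not shown.

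**Illustration of size**

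Inputs from Sample size and Setting: difference 4 kg, power 0.80, alpha 0.05 (taken as two-sided), 100 per group, ICC 0.01, dropout 20%, 260 recruited, about 18 teams. The SD is not stated and has to be back-solved.

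- SD = 4 / [(1.960 + 0.842) × √(2/100)] = 10.1 kg. Putting this back, n = 2 × (1.960 + 0.842)² × 10.1² / 4² ≈ 100 per group, the article's figure.
- Completers: 260 × 0.80 = 208, or 104 per arm; 208/18 = 11.56 per team, assuming equal teams.
- Design effect: 1 + (11.56 − 1) × 0.01 = 1.106. Effective n per arm: 104/1.106 = 94.1.
- SE of the difference: 10.1 × √(2/94.1) = 1.47 kg.

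For a spurious difference b and no true effect, the two-sided type I error is Φ(b/SE − 1.96) + Φ(−b/SE − 1.96):

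| Assumed b (kg) | b/SE | Type I error |
|---|---|---|
| 0 | 0 | 5.0% |
| 0.5 | 0.34 | 6.3% |
| 0.9 | 0.61 | 9.4% |
| 1.0 | 0.68 | 10.4% |
| 1.5 | 1.02 | 17.5% |
| 2.0 | 1.36 | 27.4% |

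The 0.9 kg row corresponds, for example, to 30% of intervention recruits being patients who would lose 3 kg anyway (0.30 × 3 = 0.9, which is 22.5% of the 4 kg target). Both inputs are assumed.

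The bias could also run against the intervention. With a true 4 kg effect and no bias, power is Φ(4/1.472 − 1.96) = Φ(0.76) ≈ 78%. If selection hid 0.9 kg of that effect, power would be Φ(3.1/1.472 − 1.96) = Φ(0.15) ≈ 56%.

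**The case against.** The strongest reply is that the timing is not documented. A reader might infer that all intervention patients are recruited after allocation by trained staff. The article does not say so. It is a condensed account, its flow figure is missing, and the remark on blinding gives the nature of the intervention as its reason; it does not say what teams knew when they drew up their lists. The training is required for at least two workers per team, and nothing states that these are the people who approach patients. All of this stands, and it limits the claim to at least part of recruitment and to a difference that can arise. It does not remove the plain sense of the training section, where already randomised teams are coached about people who have yet to join.

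A reader might also take the willingness requirement as an asymmetry in itself, or as part of the contra-indication screen. It is neither. It is an inclusion criterion common to both arms, and contra-indications are a separate exclusion.

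The analysis is not without safeguards. Prognostic variables are to be adjusted for, and PAM-13 and self-rated views on activity and nutrition are collected at baseline. These are partial proxies for readiness. PAM-13 is not named as a covariate, however, and adjustment for it would leave unmeasured differences in place.

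Finally, recruitment by the patient's own team suits a pragmatic trial. That supports having teams recruit, but it does not require that only one arm be coached in how to do it.

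**Conclusion.** The point holds as a weakness in a stated design feature: recruitment support is given to one arm only, to teams whose allocation is already set. Enrolled patients can therefore differ by arm in ways that the planned adjustment corrects only in part. The documents do not show that such a difference will occur, how large it would be, or which arm it would favour. Coaching might bring in more motivated patients or more reluctant ones, and control teams might enrol mainly their most engaged patients.

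The type I error figures (about 9% at 0.9 kg, about 17% at 1.5 kg) are illustrations. They rest on assumed bias sizes, a back-solved SD of about 10.1 kg, 18 equal teams and 208 completers. The conclusion about order rests on the wording of the training section. A flow figure showing consent before allocation would answer most of the concern, although the training wording would then need to be reconciled with it.

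**What to change.** **Teams not yet randomised.** Fix the list of eligible patients, obtain consent and take baseline measurements before that team's allocation is released; train intervention teams only afterwards. State this order in the text.

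**Training content.** Remove the material on informing and motivating prospective participants from the intervention-only training, and use one identical recruitment script in both arms.

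**Teams already randomised.** Recruit from a list fixed before allocation where one exists. Where none exists it cannot be created afterwards, so apply the common script to all patients who meet the objective criteria.

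**Analysis and reporting.** Add baseline weight and baseline PAM-13 as covariates. Report the numbers listed, approached and consented by team and arm, so that readers can judge whether recruitment differed.

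**Cost.** A short amendment that mainly re-orders existing steps, with no extra patients. Teams wait for their allocation until baseline is complete, and a short gap opens between baseline weight and the start of the intervention.

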#### Demographics

Demographic data (age, gender, ethnicity, marital status, education level, employment status, diagnosis of SMI, number of years receiving mental care in FACT-team) will be collected directly from the patient records or patient reports.

### Main study outcomes

#### Primary outcome

The primary outcome is weight loss (kg). Body weight will be measured with participants wearing light clothing (i.e. with empty pockets, no belt) and no shoes or jackets to the nearest 0.1 kg. All assessors of each FACT-team will use the same provided digital scale (Beurer GS210).

#### Clinical outcomes

Secondary clinical outcomes include body mass index (kg/m2), waist circumference (cm), lipid profiles (LDL, HDL, total cholesterol, triglycerides), glucose metabolism (serum and fasting glucose), and systolic and diastolic blood pressure. All clinical outcomes will be measured by trained mental health professional staff or trained research staff.

#### Patient reports

Quality of life will be measured using the Dutch version of the Short Form-12 (SF-12) and the EuroQol (EQ-5D-5 L). The SF-12 is a generic, reliable and validated instrument, containing 12 items derived from the Short Form-36 questionnaire [24]. The physical and mental component summary scores of the SF-12 will be used. Dutch age- and sex-standardized population norms are available [25]. Additionally, the EQ-5D-5 L scores will be used to compute quality adjusted life years (QALYs) and valuing health [26]. The EQ-5D-5 L rates self-care, mobility, pain, psychological functioning (anxiety/ depression), and usual activities on a 5-point scale. The EQ-5D-5 L health states will be converted into utility scores using the Dutch tariff [27]. QALYs will be calculated using linear interpolation between measurement points. Using the area under the curve method, QALYs were calculated by multiplying the amount of time a patient spent in a specific health state with the utility score associated with that health state. Transitions between health states will be linearly interpolated. Smoking status is based on self-report; patients will be asked if they are current smokers and, if so, how many cigarettes they smoked in the last 7 days. Additionally, at 6 months and 12 months follow-up measurements patients who mentioned to be current smokers will be asked if they want to be referred to a smoking cessation program or another kind of help for smoking cessation (such as guidance by a caregiver or physician).

Health-related self-efficacy is measured by the Patient Activation Measure (PAM-13), a reliable questionnaire which contains 13 items derived from the original PAM-22 [28]. The questionnaire assesses the participants’ self-reported knowledge, skills and confidence for health-related self-efficacy. Satisfaction and personal view with respect to physical and mental health, nutrition status, physical activity status and sleep will be asked by giving a score from zero to ten concerning the past 2 weeks.

All questionnaires will be completed on paper or digitally (if participant is in the possession of a smartphone or internet). In case participants experience concentration or cognitive problems when filling in the questionnaires, participants will be helped by their case workers or assessors to support them. Staff and assessors will be instructed on how to support a participant in filling in questionnaires without influencing the answers.

